#### Secondary outcomes and other variables

In addition to the patient’s perceived involvement, we will also investigate physicians’ perceived involvement in decision-making as a secondary outcome using the physician version of the SDM-Q-9 (SDM-Q-Doc) [39] at T1. This will refer to the perceived involvement of the inpatient physician, and any change of the treating physician during the inpatient stay will be recorded.

Apart from the potential improvement in shared-decision-making, we will investigate whether the SDM-assistant could facilitate a more appropriate selection of antipsychotic, as reflected by lower symptom severity and fewer adverse events, higher quality of life and functioning, higher treatment satisfaction and improved adherence.

We will record information about the prescribed antipsychotic medications (e.g., dose schedule, formulation, monotherapy or polypharmacy, concomitant medications) at T0, T1 and T2.

Symptom severity and improvement will be measured at T0 and T1, using the clinician-rated Positive and Negative Syndrome Scale 6-item version (PANSS-6) [40]. PANSS-6 is a recently validated abbreviated version of the original PANSS scale [41], consisting of six items of core schizophrenia symptoms (P1 = delusions, P2 = conceptual disorganization, P3 = hallucinations, N1 = blunted affect, N4 = social withdrawal, N6 = lack of spontaneity/flow of conversation) [40, 42–44]. We will also investigate the clinician-rated Clinical Global Impression-Severity and Improvement (CGI-S, CGI-I) [45], and the patient-rated Clinical Global Impression (CGI-P) [46]. In addition, we will record the length of inpatient stay at T1, and the outpatient psychiatrist will be asked at T2 to document any readmission to the hospital of the patient.

Side-effects will be recorded using items of the clinician version of the Udvalg for kliniske undersøgelser scale (UKU-SERS) [47] at T0, T1 and T2. The UKU scale consists of 48 items covering a comprehensive list of side-effects grouped in four categories, i.e., psychic, neurologic, autonomic and other side-effects. We will also evaluate two additional items about suicidality and oedema. Each item is scored from 0 to 3 based on the severity with a higher score indicating more severity [47]. It will be administered via a semi-structured interview by the study personnel. The weight of patients will be measured at T0 and T1, and we will ask the patients to report their weight at T2. Furthermore, we developed the patient-reported antipsychotic and antidepressant side-effect scale (ANTISIDES) that will be administered at T0, T1 and T2. The scale consists of 41 items covering a broad spectrum of side effects that can be caused by psychotropic drugs. Each item will be rated on a visual analogue scale from 0 “not at all” to 10 “extremely strong”, supplemented by an assessment of the impairment experienced due to the respective side effect (eAppendix 3).

We will address global functioning using the clinician-rated Social and Occupational Functioning Assessment Scale (SOFAS) [48] at T0, T1 and T2, and quality of life using the patient-reported EUROHIS-QOL [49] at T2.

Treatment satisfaction, attitudes and adherence will be measured using the patient-reported scales Questionnaire on Patients’ Treatment Satisfaction (ZUF8) [39], Medication Satisfaction Questionnaire (MSQ) [50], Drug Attitude Inventory (DAI) [51] and Medication Adherence Rating Scale (MARS) [52] at T0, T1 and T2. Physicians will also rate adherence to the medication treatment at T1 and T2 using a single question scored on a 4-point Likert scale from 1 “very good” to 4 “poor”.

Last, data about the use of the SDM-assistant (e.g., number of sessions, duration of use) will be recorded within the SDM-assistant and evaluated at T1. This information would also be helpful in assessing treatment integrity.

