## Background

A large number of antipsychotics are available for the treatment of schizophrenia with substantial differences in their side-effect profiles and smaller in efficacy [1]. This makes the selection of an antipsychotic for the individual more difficult, given also that several factors should be taken into consideration, such as patient preferences, prior experiences, side-effect profiles, comorbidities, age and sex [2–5]. This “preference-sensitive” decision requires shared-decision-making (SDM) between patients and their treating physicians [4, 6]. In addition, physician decision-making behaviours are often not evidence-based, but influenced by irrational factors [7–9], cognitive biases [10, 11], and lack of statistical knowledge [12]. Furthermore, decisions in the treatment of schizophrenia are perceived by many patients as “paternalistic” or dominated by the physician, without patients really having a choice about which drug to be prescribed [13, 14]. These aspects could lead to less optimised drug selection, poor therapeutic relationship, lower adherence and increased relapse rates [15].

In order to overcome the above defects in decision-making, we developed an evidence-based shared-decision-making assistant (SDM-assistant) for choosing antipsychotics. This newly developed tool provides a framework of shared-decision-making illustrating evidence from a network meta-analysis on the efficacy and side-effects of antipsychotics [1]. It may also overcome limitations of previous tools with limited capabilities in shared-decision-making or presenting evidence of lower quality [16]. Patients and practitioners can use the SDM-assistant as a basis of share-decision-making by discussing and navigating differences of antipsychotics. This could facilitate “better” therapy decisions (e.g., fewer adverse events) and increase patient involvement, and thus, could subsequently lead to greater patient satisfaction and, potentially, fewer rehospitalisations due to improved adherence [17, 18]. Figure 1 shows the potential outcomes of using the SDM-assistant for choosing antipsychotics, as adapted by our previous work on shared-decision making in patients with an acute exacerbation of schizophrenia [19].

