### Outcomes

Recruitment and data collection will take place at the participating wards. Baseline data will be measured at inclusion and before using the SDM-assistant (T0). Then, the aim is that patients and physicians will use the SDM-assistant at least once during inpatient stay whenever a decision on choosing an antipsychotic is warranted, but no later than three weeks after admission. Both will also be encouraged to use the SDM-assistant as often as possible. At the time of discharge from the hospital, outcomes will be measured (T1). Three months after the discharge, we will contact each patient and the treating outpatient psychiatrist via telephone and/or post in order to obtain follow-up outcome data (T2). Table 1 presents a schematic diagram of participant timeline and data collection. Scales (German versions) could be filled accordingly by patients, their treating physicians or the study personnel (e.g., clinical psychologists not involved in the treatment of the patients and trained to administer the scales). Physicians and study personnel will receive training on the use of individual scales.

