### Data analysis

The effect-size for continuous outcomes will be the mean difference (MD) and for dichotomous outcomes will be the odds ratio (OR), presented with their 95% confidence intervals. Per-protocol analysis will be conducted, i.e., by excluding patients with no outcome data, patients that do not receive at least one session of SDM-assistant, patients who moved from a ward belonging to the control group to a ward belonging to the intervention group or vice versa. There will be no imputation of missing outcome data, and observed cases will be used.

The primary outcome (SDM-Q-9 at T1) and secondary continuous outcomes will be analysed with mixed-effects linear regression models fitted with ward (cluster) as a random-effects term and with intervention/control group as a fixed-effects term. In a similar vein, dichotomous outcomes will be analysed with logistic regression models using the generalised estimating equations (GEEs).

The robustness of the results of the primary outcome will be investigated in a sensitivity analysis by adjusting for baseline covariates such as severity of illness, admission status and variables with a large baseline imbalance.

In addition, we plan exploratory subgroup analyses in order to investigate if there is potential effect-modification of patient characteristics (e.g., age, sex, symptom severity, duration of illness) on the primary outcome.

Alpha will be set at two-sided alpha of 0.05.

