## Discussion

Choosing an antipsychotic medication is an important medical decision that should require benefit-risk assessments and the active involvement of patients whenever possible (i.e., shared-decision making) [4, 5]. In order to facilitate shared-decision making for choosing antipsychotics, we developed an evidence-based shared-decision making assistant (SDM-assistant). In the planned cluster-randomised trial, we will examine the use of SDM-assistant for choosing antipsychotics in hospitalized patients with an acute exacerbation of schizophrenia. We will evaluate the perceived involvement of patients in the decision-making as primary outcome, and therapeutic alliance, symptom severity, side-effects, treatment satisfaction, adherence, quality of life, functioning and rehospitalizations as secondary outcomes.

There are potential methodological limitations and challenges.

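### Readmission has one named informant, the outpatient psychiatrist, so readmissions are likely to be undercounted and the comparison could be biased if loss of contact differs by arm

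*Protocol article*

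**What the plan says.** Under Secondary outcomes and other variables, the article assigns readmission to one informant: "the outpatient psychiatrist will be asked at T2 to document any readmission to the hospital of the patient". The same section names the patient as the source of a different T2 item: "we will ask the patients to report their weight at T2". Under Outcomes, the T2 contact is described in general terms: "we will contact each patient and the treating outpatient psychiatrist via telephone and/or post in order to obtain follow-up outcome data (T2". That sentence does not say which informant supplies which outcome.

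The Discussion lists "functioning and rehospitalizations as secondary outcomes", and its closing paragraph puts rehospitalisation among the outcomes meant to show that antipsychotics were better chosen. The Background gives the expected route: "fewer rehospitalisations due to improved adherence".

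Under Data analysis, "Per-protocol analysis will be conducted, i.e., by excluding patients with no outcome data", and "There will be no imputation of missing outcome data, and observed cases will be used". Dichotomous outcomes are summarised by an odds ratio from a logistic GEE model.

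**The concern.** Whether readmission is known for a patient depends on that patient having an outpatient psychiatrist who is still in touch. Two things can go wrong. If no psychiatrist answers, the patient has no readmission outcome and leaves the analysis. If the psychiatrist answers without knowing of an admission, the patient is counted as not readmitted.

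Both errors lower the number of readmissions found, and the first also costs precision. Whether they distort the comparison depends on the arms. If the intervention changes how many patients stay in outpatient contact, or which ones, the readmission data in the two arms come from differently selected patients. An analysis plan cannot repair this later, because the data would never have been collected.

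**Working it through.** The article gives no readmission rate, effect or power, so there is no stated figure to reproduce. What follows is an illustration.

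**Inputs from the article:** 126 patients per arm and an assumed patient drop-out of 15–25% (Sample size and recruitment); observed cases only, odds ratio as effect measure (Data analysis).

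**Assumed inputs:** readmission risk in patients with an informed psychiatrist (r_in) and without one (r_out), the same in both arms; the proportion without one in control (q_C) and intervention (q_I). Everyone without an informed psychiatrist is first treated as missing.

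**Formulae:** true risk = (1 − q) × r_in + q × r_out. Observed-case risk = r_in. Share of readmissions missed = q × r_out ÷ true risk.

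**Worked case** (r_in 15%, r_out 35%, q_C 25%, q_I 15%):
- Control: 0.75 × 0.15 + 0.25 × 0.35 = 0.20
- Intervention: 0.85 × 0.15 + 0.15 × 0.35 = 0.18
- True odds ratio: (0.18/0.82) ÷ (0.20/0.80) = 0.88
- Observed cases: 15% in both arms, odds ratio 1.00
- Readmissions unseen: 126 × 0.25 × 0.35 = 11.0 in control; 126 × 0.15 × 0.35 = 6.6 in intervention

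**Range:**

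| r_in / r_out | q_C / q_I | True risk C / I | True OR | Observed OR | Control readmissions missed |
|---|---|---|---|---|---|
| 15% / 35% | 25% / 25% | 20.0% / 20.0% | 1.00 | 1.00 | 44% |
| 15% / 35% | 25% / 15% | 20.0% / 18.0% | 0.88 | 1.00 | 44% |
| 15% / 35% | 30% / 10% | 21.0% / 17.0% | 0.77 | 1.00 | 50% |
| 15% / 45% | 25% / 25% | 22.5% / 22.5% | 1.00 | 1.00 | 50% |
| 15% / 45% | 25% / 15% | 22.5% / 19.5% | 0.83 | 1.00 | 50% |
| 15% / 45% | 30% / 10% | 24.0% / 18.0% | 0.70 | 1.00 | 56% |
| 20% / 30% | 25% / 25% | 22.5% / 22.5% | 1.00 | 1.00 | 33% |
| 20% / 30% | 25% / 15% | 22.5% / 21.5% | 0.94 | 1.00 | 33% |
| 20% / 30% | 30% / 10% | 23.0% / 21.0% | 0.89 | 1.00 | 39% |

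The observed odds ratio is 1.00 by construction, because the within-stratum risks are set equal across arms. The table shows what unequal loss can hide, not what it will hide. With equal loss the odds ratio is unbiased in this set-up and the harm is undercounting.

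**If the same patients are instead recorded as not readmitted** (worked case, extreme): control 0.75 × 0.15 = 11.25%, intervention 0.85 × 0.15 = 12.75%. The odds ratio is (0.1275/0.8725) ÷ (0.1125/0.8875) = 1.15, on the other side of 1 from the true 0.88.

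**Bounds without a model for the missing patients**, assuming the 15–25% drop-out applies to readmission status and about 15% of observed patients are readmitted:
- 15% loss: 19 unknown and 16 of 107 readmitted per arm. If all unknowns in control and none in intervention were readmitted, the odds ratio is (16/110) ÷ (35/91) = 0.38; reversed, 2.64.
- 25% loss: 32 unknown and 14 of 94 readmitted per arm. The bounds are (14/112) ÷ (46/80) = 0.22 and, reversed, 4.60.

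Observed cases would give 1.00 in both.

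**The case against.** The article does not say that the psychiatrist is the sole source. Patients are contacted at T2 as well, Table 1 with the data collection schedule is not shown, and the article condenses a fuller protocol. A patient question or record check may exist there. This stands as a limit: the point concerns the visible text. The silence still counts for something, because the same section does name the patient as the source of T2 weight.

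A reader might infer that patients out of outpatient care are known to be at high risk, that missingness is tied to the arm, and that a benefit on readmission would be invisible. The documents do not support that. They give no risk for such patients. The adherence they measure is adherence to medication, and keeping patients in outpatient care is neither a stated target nor an outcome. The Background's link between poorer decision-making, lower adherence and relapse makes a dependence plausible, no more. A benefit acting through better adherence in patients still in contact would be seen.

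The hidden effect is also small against the trial's precision. In the worked case the difference is 2 points, while the 95% half-width is 1.96 × √[(0.20 × 0.80 + 0.18 × 0.82)/126] = 9.7 points before clustering or loss. That bears on priority, and the undercount remains.

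Finally, observed-case analysis applies to every outcome. True, but readmission is an event that hospital records can document without the patient or psychiatrist replying, so here much of the gap can be avoided.

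**Conclusion.** The point holds in a limited form. Followed as written, the text makes knowledge of readmission depend on one informant whose availability varies with the patient's contact with outpatient care. Undercounting is likely: a third to a half of readmissions at 25% loss in both arms, on the assumed risks above. Bias in the odds ratio is possible rather than shown. It needs loss of contact, or its relation to readmission, to differ by arm; across the assumed range with unequal loss, true odds ratios of 0.70 to 0.94 all appeared as 1.00. Every rate behind these figures is an assumption.

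The consequence is confined to a secondary outcome. The primary outcome, SDM-Q-9 at discharge, and the sample size built on it are untouched. This is a worthwhile, inexpensive improvement and not a flaw that threatens the trial.

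**What to change.** - At T2, ask every patient about any readmission since discharge, in the contact already planned, alongside the question to the outpatient psychiatrist.
- Subject to consent and data protection, check the admission records of the three participating hospitals for every patient. The terms of the consent are not shown, so its coverage must be confirmed first.
- Count a readmission if any source confirms it. Apply the same sources and rule in both arms, which matters because the wards are not blinded.
- Record which source supplied the information, state beforehand when status counts as unknown, and report the number unknown by arm.

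If Table 1 or the full protocol already provides for these sources, it is enough to say so in the text.

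The cost is one extra question, a record look-up and possibly a line on consent. Design, sample size and primary analysis do not change. Admissions to other hospitals would still rest on what patients and psychiatrists report.

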#### Qualitative data

We will also obtain qualitative data in order to gain insights into the treatment integrity and mode of action of using the SDM-assistant for choosing antipsychotics, as well as identify further potential influencing factors. The combination of quantitative (hypothesis-driven) and qualitative approach would increase the validity and interpretation of the findings of the trial. For this purpose, we will use purposive sampling in order to identify individual cases of successful/unsuccessful joint decisions or antipsychotic selection. We will conduct interviews with about 15 patients from the intervention group until no fundamentally new aspects will be added. Possible inclusion criteria are as follows: 1) patient or physician are dissatisfied with the use of SDM-assistant and/or do not want to use it in the future, 2) patient or physician discontinue the use of SDM-assistant, 3) patient or physician disagree with the outcome of the SDM-assistant. 4) patient or physician satisfaction with the SDM-assistant is far above average, 5) the use or the outcome of the SDM-assistant triggers unusual or unexpected reactions in the patient or physician. Physicians will be interviewed separately and in terms of their experience across several uses of the app with their patients. The interviews will be guideline-based and conducted by the study personnel, recorded acoustically, then transcribed and qualitatively analysed using content analysis [53].

### Sample size and recruitment

The target sample size is *N* = 252 patients from *n* = 14 clusters (126 participants from 7 intervention wards and 126 participants from 7 control wards). Power calculation estimated *N* = 180 participants (*n* = 12 clusters) to be analysed in order to detect an expected Cohen’s d of 0.45–0.5 in the primary outcome of SDM-Q-9 with a power of at least 80% at two-sided alpha of 0.05 assuming ICC = 0.02. These assumptions are based on data from a comparable study (SDM-PLUS), which involved a similar population and the same main outcome parameter [38]. Due to an assumed drop-out rate of patients of 15–25% and to account for a potential drop out of clusters, we aim at recruiting *n* = 14 clusters and *N* = 252 patients.

Patient recruitment will be conducted by a trained study staff and will take place on the 14 selected wards at three hospitals in Munich, Germany (Klinikum rechts der Isar of the Technical University of Munich, kbo-Isar-Amper-Klinikum München-Ost and München-Schwabing). These hospitals with more than 1500 beds in total can facilitate the enrolment of the planned number of patients (*N* = 252) in a timely manner, as in our previous trials [38, 54].

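### The stated power of at least 80% for d = 0.45–0.5 with 180 patients in 12 wards fails at the lower end of that range: it is 76% at d = 0.45 and 84% at d = 0.5 by the normal approximation, and lower if small-sample degrees of freedom are used

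*Protocol article*

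**What the plan says.** Under Sample size and recruitment, the protocol article gives the calculation in one sentence: "Power calculation estimated *N* = 180 participants (*n* = 12 clusters) to be analysed", for a Cohen's d between 0.45 and 0.5 "in the primary outcome of SDM-Q-9 with a power of at least 80% at two-sided alpha of 0.05 assuming ICC = 0.02". The recruitment target is then set higher, at 252 patients in 14 wards ("126 participants from 7 intervention wards and 126 participants from 7 control wards"), and the reason given is this: "Due to an assumed drop-out rate of patients of 15–25% and to account for a potential drop out of clusters". The power figure itself is attached to the 180 patients and 12 wards.

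Under Data analysis, the primary outcome is to be analysed by a linear mixed model with a random ward effect and a fixed group effect. There is no pair term, and no degrees-of-freedom method is named. The significance level is repeated there: "Alpha will be set at two-sided alpha of 0.05".

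**The concern.** A claim of at least 80% power over a range of effects has to hold at the smallest effect in the range, where power is lowest. Here every input is printed in one sentence, so the claim can be checked without any outside figure.

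The power figure justifies the size of the trial and informs how a non-significant result is read. The sentence implies at most a 20% chance of missing any effect in the range that the sponsor expects. If the true figure at d = 0.45 is 76%, that chance is 24%. If the test also pays for the small number of wards, it is 33%.

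**Working it through.** **Inputs**
- 180 analysed patients in 12 wards, ICC 0.02, d = 0.45–0.5, 80% power (Sample size and recruitment); two-sided alpha 0.05 (same section and Data analysis).
- Equal arms, as in the recruitment target: 6 wards and 90 patients per arm.
- Equal ward sizes, 180/12 = 15 per ward. This is an assumption; unequal sizes would lower power further.

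**1. The stated figure, by the normal approximation**
- Design effect = 1 + (15 − 1) × 0.02 = 1.28.
- Effective patients per arm = 90/1.28 = 70.3.
- Noncentrality = d × √(70.3/2) = d × 5.929, which is 2.668 at d = 0.45 and 2.965 at d = 0.5.
- Power = Φ(noncentrality − 1.960): Φ(0.708) = 76.1% at d = 0.45 and Φ(1.005) = 84.2% at d = 0.5. At d = 0.475 it is 80.4%.
- Smallest d with 80% power = (1.960 + 0.842)/5.929 = 0.473.

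The stated figure is therefore met in the upper part of the range and missed in the lower part. A t-test on 178 degrees of freedom changes little (75.6% and 83.9%).

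The same formula solved for sample size agrees. At d = 0.45, 2 × 2.802²/0.45² = 77.5, so 78 per arm before clustering, and 78 × 2 × 1.28 = 199.7, or 200 patients. At d = 0.5 it is 63 × 2 × 1.28 = 161.3, or 162 patients. A total of 180 fits an effect near the middle of the range.

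**2. Could other inputs explain 80% at d = 0.45?** A one-sided alpha of 0.05 gives 84.7%, and ignoring the ICC gives 85.5%. Both contradict the stated inputs.

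**3. With small-sample degrees of freedom (assumption)**

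Treatment is assigned by ward, so in the unpaired model of the Data analysis section the group effect is a between-ward contrast with 12 − 2 = 10 degrees of freedom. With critical value 2.228 and the noncentralities above, the noncentral t distribution gives 67.3% at d = 0.45 and 76.2% at d = 0.5. Simulating a t-test on ward means (200,000 runs) gives the same two figures. Power of 80% is reached at d = 0.525.

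**4. With a Wald z-test from the mixed model.** In simulation (balanced wards, REML-type variance estimate) power is 74% at d = 0.45 and 82% at d = 0.5, with type I error of about 5.5–5.6%. The lower end again misses 80%.

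**5. The recruited design, no ward lost**

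Drop-out of 25% leaves 252 × 0.75 = 189 patients (13.5 per ward, design effect 1.25). Drop-out of 15% leaves 252 × 0.85 = 214 (15.3 per ward, design effect 1.286).

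| Design | Method | d = 0.45 | d = 0.5 |
|---|---|---|---|
| 12 wards, 180 analysed | normal | 76% | 84% |
| 12 wards, 180 analysed | t, 10 df | 67% | 76% |
| 14 wards, 189–214 analysed | normal | 79–83% | 87–90% |
| 14 wards, 189–214 analysed | t, 12 df | 72–76% | 81–84% |

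**The case against.** Four points can be made for the plan.

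- *The shortfall is small.* By the conventional formula it is about 4 percentage points at one end of a range, and 80% is reached at d = 0.473, inside that range. This stands and limits the weight of the point. It does not make the sentence right, because the sentence claims at least 80% for the range, not about 80% at its middle.
- *The planned trial is larger than the 12-ward case.* With all 14 wards kept, the normal approximation gives 79–83% at d = 0.45. This stands as reassurance about the trial, but the article attaches its power to 180 patients in 12 wards and uses the surplus to cover losses.
- *Degrees of freedom belong in an analysis plan.* This also stands. A reader might infer from the 10-df figures that the trial is below 80% across the whole range. The documents do not support that as a finding of error: no degrees-of-freedom method is stated, and by the normal approximation power at d = 0.5 is 84%. The 67% and 76% show what a common small-sample test would deliver; they do not correct a figure in the protocol.
- *A null result need not mislead.* The article commits to 95% confidence intervals, which show directly which effects remain compatible with the data. So it should not be said that a null result would be taken to exclude effects of this size.

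**Conclusion.** The statement is wrong as written, to a modest degree. For 180 patients in 12 wards with ICC 0.02 and two-sided alpha 0.05, power is 76% at d = 0.45 and 84% at d = 0.5, so at least 80% holds only from d = 0.473. This rests on the article's own inputs, equal arms and equal ward sizes, and on the most favourable standard method.

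Conditional on a t-test with 10 degrees of freedom, power is 67% and 76%, and 80% requires d = 0.525. Ten is the natural between-ward value for the unpaired model described, but it is an assumption here.

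This is a restatement that should be made. It does not show that the trial is too small to run.

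**What to change.** Replace the power statement with figures that name the method, for example:

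> With 180 analysed patients in 12 wards (ICC 0.02, two-sided alpha 0.05), power is 76% at d = 0.45 and 84% at d = 0.5 by the normal approximation (80% at d = 0.473), and 67% and 76% with a t-test on 10 degrees of freedom (80% at d = 0.525). With 14 wards, no ward lost and 15–25% drop-out (189–214 analysed), power is 79–83% at d = 0.45 and 87–90% at d = 0.5 by the normal approximation, and 72–76% and 81–84% on 12 degrees of freedom.

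Once the analysis method is settled, only the matching set of figures need stay.

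Because wards are matched, it may be tempting to say that a pair term would win back the power. That should not be claimed. Six pairs leave 5 degrees of freedom, which gives 57% at d = 0.45 and 66% at d = 0.5 if pairing removes no variance. With an ICC of 0.02 there is little between-ward variance to remove.

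The change is to text only and adds no patients or wards. Its cost is a less favourable stated power.

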### Participants

Participants should have a diagnosis of a schizophrenia spectrum disorder (ICD-10 F20-F9) and be hospitalized in an acute psychiatric ward at the time of examination. They should be aged between 18 and 65 years at the time of inclusion and be able to give their informed consent to participate in the study. There are no other exclusion criteria, e.g., in terms of sex, ethnicity, illness stage.

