### Randomization and blinding

Randomization will take place at the cluster (i.e., ward) level, in order to minimize contamination effects inherent to the nature of the intervention in case the randomization was performed at the patient or physician level [55]. The investigators will determine seven pairs of comparable wards (regarding the treatment spectrum, the size of the ward, etc.) and then randomize one ward of each pair either to the intervention or to the control group. While the principal investigators will determine the paired wards, the randomization will be conducted by a blinded investigator independent to the study using the coin toss method. However, due to the nature of the intervention (use of the SDM-assistant vs. TAU), there will be no blinding between intervention and control wards.

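### Patients are enrolled on openly randomised wards, so selection after allocation can enter the primary estimate, yet baseline adjustment is left to a loosely specified sensitivity analysis

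*Protocol article*

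**What the plan says.** All references are to the Protocol article.

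- **Allocation** (Randomization and blinding). "Randomization will take place at the cluster (i.e., ward) level, in order to minimize contamination effects". Seven matched pairs are formed, and "the randomization will be conducted by a blinded investigator independent to the study using the coin toss method". Once wards are allocated, "there will be no blinding between intervention and control wards".
- **Enrolment** (Sample size and recruitment; Participants; Outcomes). "Patient recruitment will be conducted by a trained study staff and will take place on the 14 selected wards". Patients must "be hospitalized in an acute psychiatric ward at the time of examination" and "be able to give their informed consent to participate in the study". Diagnosis and an age of 18 to 65 are also required. Beyond that, "There are no other exclusion criteria, e.g., in terms of sex, ethnicity, illness stage". T0 is taken at each patient's inclusion, before the tool is used, and first use is due within three weeks of admission.
- **Baseline measures** (Baseline parameters; Secondary outcomes and other variables). T0 includes legal status, voluntary or involuntary treatment, Birchwood insight, the participation subscale of the Autonomy Preference Index, the MacArthur admission survey and PANSS-6.
- **Analysis** (Data analysis). The primary SDM-Q-9 model is "fitted with ward (cluster) as a random-effects term and with intervention/control group as a fixed-effects term". A sensitivity analysis adjusts for baseline covariates. Severity and admission status are given as examples, and any variable showing a large imbalance at baseline is added.

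**The concern.** In a cluster trial, randomising wards balances wards in expectation. It balances patients only if they enter both arms by the same process. Here the person tossing the coin is blinded, which conceals the allocation of wards but not the later enrolment of patients.

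The Discussion supplies a plausible mechanism. It names reduced decisional capacity, severe symptoms, poor insight and negative attitudes to treatment as obstacles to shared decision-making, and says the tool may add to the demands on patients. Such traits could affect who is approached, who is judged able to consent and who agrees. They could do so differently on a ward where the tool is in use and on one where it is not. If they also relate to the SDM-Q-9, a patient-reported score in an open trial, the arm difference mixes selection with the effect of the tool.

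At stake is how the primary result can be read. A positive finding could be partly selection. If selection ran the other way, a real effect could be masked.

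**Working it through.** **1. The plan's own figure.** Inputs from Sample size and recruitment: 180 analysed in 12 wards, d 0.45–0.5, two-sided alpha 0.05, power at least 80%, ICC 0.02.

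- Patients per ward: 180/12 = 15. Design effect: 1 + (15 − 1) × 0.02 = 1.28.
- At the midpoint d = 0.475, n per arm = 2 × (1.960 + 0.842)² / 0.475² = 69.6, so 70. Total: 2 × 70 × 1.28 = 179, which matches 180.
- Power at 180 (normal approximation) is 76% at d = 0.45, 80% at 0.475 and 84% at 0.50. The stated figure is thus reproduced at the midpoint, and its standard error can be used below.

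**2. Standard error of the standardised arm difference.** SE = √(4 × 1.28 / 180) = 0.169 SD.

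**3. Type I error if selection shifts the arm difference by b.** With no true effect, the test statistic centres on b/SE. The two-sided rejection probability is 1 − Φ(1.960 − b/SE) + Φ(−1.960 − b/SE). The last column uses a t reference with 12 − 2 = 10 degrees of freedom. The shifts are assumptions, because the document gives none.

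| Shift b (SD) | b/SE | Share of d = 0.45 | Type I error, normal | Type I error, t(10) |
|---|---|---|---|---|
| 0 | 0 | 0% | 5.0% | 5.0% |
| 0.05 | 0.30 | 11% | 6.0% | 5.8% |
| 0.10 | 0.59 | 22% | 9.1% | 8.4% |
| 0.15 | 0.89 | 33% | 14.4% | 12.7% |
| 0.20 | 1.19 | 44% | 22.0% | 18.9% |

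**4. What could produce such a shift (assumed scenarios).** Suppose a share p of eligible patients would score 1 SD lower than the rest. One arm enrols all of them and the other enrols a fraction k. The shift is b = p − pk/(pk + 1 − p).

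- p = 0.20, k = 0.5: 0.20 − 0.10/0.90 = 0.089 SD, type I error about 8%.
- p = 0.30, k = 0.5: 0.30 − 0.15/0.85 = 0.124 SD, type I error about 11%.
- p = 0.20, k = 0.75: 0.20 − 0.15/0.95 = 0.042 SD, type I error about 6%.

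Mild differential enrolment does little harm; moderate differential enrolment roughly doubles the error rate.

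**5. Why the primary model does not absorb the shift.** The ward random effect represents variation between wards within an arm. A shift common to the wards of one arm is aligned with the arm term and is estimated as treatment effect. More patients would not help: SE falls while b stays the same.

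**The case against.** **Sequence and knowledge are inferred.** The article never says outright that recruitment follows randomisation or that recruiters know the arm. That is correct. The inference is nevertheless strong: patients are found during acute admissions, tool use is due within three weeks of admission, physicians are trained on the tool at the outset, and the wards are not blinded.

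**The plan already measures and adjusts.** This stands in large part. A reader might infer that nothing is done to detect or offset selection, but the T0 battery and the adjusted sensitivity analysis contradict that. What remains is that the adjustment is not primary, that its covariates are only examples, that insight and participation preference are not named, and that further covariates enter after imbalance has been seen.

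**Ward randomisation protects the comparison.** It does protect against ward-level confounding, and a reader who concluded that it offers no protection would go too far. It does not cover the selection of patients afterwards.

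**Direction is speculative.** Agreed. It is tempting to say that intervention wards will enrol more cooperative patients and so mimic a benefit. The same consent criterion applies in both arms, however, and a decision tool might equally attract patients who feel excluded from decisions. The document settles neither direction nor size.

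**Screening rules, staffing rotas and logs belong to the full protocol.** This largely stands. Their absence from an article is not a finding. Withholding the ward's arm until after T0 may also be impracticable where the tool is in open use.

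**Conclusion.** The concern holds in a limited form. Open ward allocation combined with individual enrolment leaves room for differential patient selection, and the primary model would pass any such difference straight into the SDM-Q-9 estimate. The variables that could reduce it are already collected but are kept out of the primary analysis.

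The size is conditional: about 9%, 14% or 22% type I error for assumed shifts of 0.10, 0.15 or 0.20 SD (8%, 13% or 19% with t on 10 df). This rests on 180 analysed, 12 equal wards and ICC 0.02. These figures show how sensitive the trial is to selection. They are not evidence that selection will occur.

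A separate issue can compound this one: the per-protocol rule excludes patients without an SDM-assistant session, a further selection after allocation that bears on the intervention arm.

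**What to change.** **Main change, in Data analysis.** Prespecify T0 PANSS-6, admission (legal) status, Birchwood insight and the Autonomy Preference Index as fixed covariates in the primary SDM-Q-9 model. Make the arm-and-ward model the sensitivity analysis. Remove the selection of covariates by observed baseline imbalance.

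**Supporting step, if the full protocol does not already provide for it.** Apply the same consecutive-screening rule on both wards of a pair. Report by arm the numbers screened, judged unable to consent, declining and enrolled.

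**Cost.** No extra patients and no new measurements. The model uses a few more degrees of freedom. Because the plan uses observed cases without imputing outcomes, patients with a missing T0 value would drop out of the adjusted model unless a rule for missing covariates is set. The log takes some staff time. Adjustment deals only with selection on measured variables; the screening counts help a reader judge how much may remain.
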